# Family health partners in regional network structures (NEST): A non-randomized controlled trial among parents of chronically ill and disabled children

**DOI:** 10.1371/journal.pone.0288435

**Published:** 2023-07-17

## Abstract

**Background:**

The overarching project goal is to evaluate the effectiveness of a cross-sectoral and cross-service provider offering professional support for families with chronically ill and disabled children: so-called Family Health Partners (in German: ‘Familien-Gesundheits-Partner’ or FGP). This needs-oriented service, which is anchored in regional networks, aims to provide ‘holistic’ support for families with children in need of care.

**Methods:**

We are carrying out a non-randomized controlled trial with four points of measurement (t0-t3 in 18 months), beginning in January 2022. Both intervention and control group include 102 families. Primary outcome measure is the quality of life, secondary outcomes are resilience factors and associated measures as well as the access to care. Multilevel regression models will be used to analyze the longitudinal data.

**Discussion:**

The strength of this study is that it looks at the health and resilience of all family members involved by examining how a FGP can influence the entire family system with regard to increasing quality of life, resilience and self-efficacy. The network structures of FGP also open up better to previously unknown regional supply offers. There are, however, a number of limitations (e.g. type of outcomes, sample size).

**Trial registration:**

This study was first registered on the German Clinical Trials Register before enrolment of participants started (ID: DRKS00027465, 4 January 2022). In order to promote its dissemination, it was also retrospectively registered on ClinicalTrials.gov (ID: NCT05418205, 14 June 2022).

## Introduction

The NEST project (German acronym for, Strengthening and relief for families with children in need of care through family health partners in regional NEtwork STructures‘) starts facing the problem that families with children with severe health problems due to disability or chronic illness are exposed to strong emotional, social, economic and temporal burdens [1–7]. These burdens result in further health, social and economic risks [8–14], which often lead to fragile living and burdening care situations for the families concerned [15]. This is, among other things, also due to legal regulations that do not do justice to the respective individual life situation and the lack of competent counseling services [16].

The overarching objective of the project is the implementation and evaluation of an innovative support service that addresses the problem. The support by so-called Family Health Partners (in German: ‘Familien-Gesundheits-Partner’ or FGP) aims to provide needs-based, individual counseling for all members in affected families to reach the best possible physical, psychological and participation-oriented care for children in need of care; and thus relieving the family members who spend much time for care and assistance of their child. The intervention to be evaluated here with regard to its effectiveness (processes and structures) was summarized in line with the terms of FGP. This personalized approach, which is embedded in the regional network, aims to provide “holistic” support for families with children in need of care. This means that the needs of the families are defined individually and independent of sectoral or service provider specific offers (structured assessment).

The needs of families not only relate to medical, nursing or therapeutic care, but also to assistance regarding social law, economic and bureaucratic advice as well as addressing social, psychosocial and emotional needs and social participation. Based on the identified need for support, affected families are individually accompanied by FGP over a certain period of time (in the project context: more than four times a year). The medium-term goal of FGP support is to strengthen or preserve the family as a self-help system, i.e. self-efficient, independently acting primary resource for the care and support of their children (preventive).

### Hypotheses

The development and systematic establishment of the three FGP core processes of a) structured assessment of the needs and requirements of families, b) counseling and coordination function and c) opening up accesses to needs-based support and relief offers in the regional supply network greatly contrast with the regular supply:

better recognition of the needs and requirements of families with children in need of care, across service providers and payers, and thus being addressed in a targeted and timely manner;more relief for families with children in need of care, and family care system strengthened;improved health, care and quality of life for families and children in need of care.

In the quantitative research part of the project, a prospective design is used to examine whether and to what extent the FGP intervention, coordination and family support as well as network support is suitable for achieving the care goals. Hypotheses are that through the intervention:

Access to care for families with children in need of care is improved.Over-, under- and misuse of health services is avoided.The family is strengthened as the most important resource for quality of life.

## Materials and methods

### Design

A non-randomized controlled study (quantitative online survey) over 18 months is ongoing with four measurement points: baseline at the start of the intervention (t0), interim assessments after 6 (t1) and 12 (t2) months, and a final survey after 18 months (t3). In order to be able to identify at least medium effects (Cohen’s d = 0.5) [17] with a test power of 0.80 and an alpha error of 0.05, at least 52 families both from the intervention and control group are required to participate in the study. Since there are hardly any longitudinal intervention studies with particular regional differences in the field of self-help research, the extent of the regional variance (hierarchical data structure) can only be estimated. Assuming 5% intracluster variance explained by the hierarchical data structure, this sample size must be increased by the variance inflation factor [18], resulting in a minimum of 73 families per group. With an estimated drop-out rate of 20–40% based on current studies (e.g. Recapture Life-AYA study [19]), the number of samples ultimately increases to a total of N = 204 families.

The study is conducted with parents and other guardians (all genders and ethnicities) with at least one disabled and/or chronically ill child under 18 years (benefit receipt according to § 37 of Germany’s Social Security Code V and/or level of care > 1), and is limited to the main adult caregivers of the child. The families from the intervention group are recruited via the care service ‘nestwärme gGmbH’ and its network partners in three metropolitan areas of Germany (Trier, Saarbrucken and Munich). The families for the control group are recruited via the umbrella organization ‘Kindernetzwerk e.V.’, which also has regional associations in these regions. In contrast to the control group, which is supported by standard care, the intervention group receives an FGP that carries out a structured assessment in the family and accompanies the family throughout the intervention period. Recruitment for the baseline data collection already started in the intervention areas in January 2022. Control group participants were recruited throughout Germany, with 102 families consenting to take part in the study until the end of September 2022.

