### Statistical analysis

SPSS™ 27 and the programming language R are used as software for the statistical analyzes. In the first step at baseline, the data analysis is primarily descriptive according to sample characteristics and outcome measures. Subgroup analyzes between intervention and control group are made using Chi^2^ test, t-test and Mann-Whitney U test, based on the measurement/scales of the related variables. Multilevel regression models will be used to analyze the longitudinal data. This makes it possible to statistically model and control regional differences. Interaction effects are calculated to analyze group differences (intervention vs. control).

If the proportion of missing values (e.g. "don’t know", no answer) is lower than 5%, these will be excluded from the analysis in accordance with the GESIS guidelines [34]. Else, for larger proportions missing data will be imputed using the multivariate imputation by chained equations method [35].

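### The starting figure of 52 families per group gives 80% power for d = 0.5 only with a one-sided 5% test or an unstated within-family correlation; a simple two-sided comparison needs 64

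*Protocol article*

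**What the plan says.** The sample-size paragraph is in the Design section of the protocol article. Its target is given as "In order to be able to identify at least medium effects", quantified as Cohen's d = 0.5, "with a test power of 0.80 and an alpha error of 0.05". From these inputs it concludes that "at least 52 families both from the intervention and control group are required to participate in the study".

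Two inflation steps follow. "Assuming 5% intracluster variance explained by the hierarchical data structure", the requirement rises to 73 per group. An expected drop-out of 20–40% then takes it to 204 families in total. The abstract matches this: "Both intervention and control group include 102 families".

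The article does not say whether alpha is one- or two-sided, which test the calculation refers to, or whether a correlation between repeated measurements was assumed. The Hypotheses section is worded directionally, for example "Access to care for families with children in need of care is improved". The Statistical analysis section plans multilevel regression with interaction effects for the longitudinal data and states no sidedness.

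**The concern.** An alpha of 0.05 given without qualification is normally read as two-sided. On that reading, the textbook requirement for d = 0.5 at 80% power is 64 per group, and 52 falls clearly short. The figures of 73 and 204 are obtained by multiplying up from 52, so a shortfall at the start is not repaired later.

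Two things are at stake. If the analysis is two-sided and no correlation was assumed, the trial is described as having 80% power when it has less, and a null result would be read against a power claim that the stated inputs do not support. If a one-sided 5% test was intended, the chance of a false claim of benefit is 5% instead of the conventional 2.5%, and readers are not told so.

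**Working it through.** **Inputs from the Design section:** d = 0.5, power 0.80, alpha 0.05, 52 per group, then 73 per group, drop-out 20–40%, total 204. **From the abstract:** 102 per group, so allocation is 1:1. **Assumption:** a comparison of two independent means, because the article names no test for the calculation.

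**1. Reproducing 52.** The normal approximation is n per group = 2 × ((z_alpha + z_power) / d)², with z_power = 0.842.

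- One-sided 5% (z_alpha = 1.645): 2 × ((1.645 + 0.842) / 0.5)² = 49.5, so 50.
- Two-sided 5% (z_alpha = 1.960): 2 × ((1.960 + 0.842) / 0.5)² = 62.8, so 63.

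The exact t-test, and the t-test figure divided by the Mann-Whitney efficiency of 0.955, give:

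| Test | One-sided n per group | Two-sided n per group |
|---|---|---|
| Normal approximation | 50 | 63 |
| t-test | 50.2, so 51 | 63.8, so 64 |
| Mann-Whitney | 52.5, so 53 | 66.8, so 67 |
| t-test power at n = 52 | 0.813 | 0.714 |

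The one-sided results lie within 2 of the printed 52. No two-sided result comes near it.

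**2. Following the chain.** 73 / 52 = 1.404, and 52 × 1.4 = 72.8, which rounds up to 73. The inflation factor is therefore about 1.4. Next, 1 − 73/102 = 0.284, so 102 per group corresponds to about 28% drop-out, inside the stated 20–40%. Both later figures are thus multiples of 52.

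**3. What 102 per group delivers.** Effective n per group = 102 × (1 − drop-out) / 1.4. Power is for d = 0.5 with a simple two-group t-test at alpha 0.05.

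| Drop-out | Effective n | Power, two-sided | Power, one-sided | Detectable d at 80%, two-sided |
|---|---|---|---|---|
| 20% | 58.3 | 0.763 | 0.850 | 0.52 |
| 30% | 51.0 | 0.706 | 0.806 | 0.56 |
| 40% | 43.7 | 0.637 | 0.750 | 0.61 |

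**4. The plan's own route started from 64.** 64 × 1.4 = 89.6, so 90 per group after clustering. Then 90 / 0.8 = 112.5, so 113 per group at 20% drop-out, and 90 / 0.6 = 150 at 40%.

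**5. Could repeated measurements explain 52 two-sided?** The article gives no within-family correlation r, so the r that turns 64 into 52 must be solved for each contrast:

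- Follow-up adjusted for baseline: 64 × (1 − r²) = 52 gives r = √0.1875 = 0.43.
- Change from baseline (group-by-time over two waves): 64 × 2(1 − r) = 52 gives r = 0.59.
- Average group difference over four waves: 64 × (1 + 3r)/4 = 52 gives r = 0.75.

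Each is possible. None is stated. For the change contrast, r below 0.5 makes power lower than in the simple comparison, so the effect could go either way.

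**The case against.** The strongest objection is that two-sided testing is not in the document. The Design section says only "an alpha error of 0.05", the hypotheses are directional, and 52 is close to what a one-sided 5% test requires. A reader might infer that 52 is a plain miscalculation and that 73 and 204 rest on about 71% power. The document does not support that inference. It holds only if testing is two-sided and the calculation was a simple two-group comparison, and neither is stated.

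A reader might also point to the sentence "Subgroup analyzes between intervention and control group are made using Chi^2^ test, t-test and Mann-Whitney U test" as evidence of two-sided testing. That sentence follows directly on the baseline step and appears to describe baseline comparisons, not the test of the intervention effect. That such tests and regression terms are two-sided by default is a software convention, not something the plan says.

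It is also true that the planned analysis is a multilevel model with interaction effects. Power of 0.71 belongs to an unadjusted comparison at one wave, so it cannot be called the power of the analysis that will be run. At 52 per group, a two-sided longitudinal contrast reaches 80% with a correlation of about 0.44 (baseline-adjusted) or 0.6 (change).

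Finally, a condensed article may leave the test and its sidedness to a fuller document. Silence alone would be no finding. But the article prints the inputs and the result, and under the usual reading of those inputs the result does not follow. Directional hypotheses do not declare a one-sided test, and an unstated correlation cannot support a printed figure.

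**Conclusion.** The point holds in a conditional form. With the printed inputs, 52 per group gives 80% power only under a one-sided 5% test (51 needed, power 0.81 at 52) or with a repeated-measures correlation that the article does not state. For a simple two-sided 5% comparison 64 are needed, and 52 gives about 0.71. The figures of 73 and 204 inherit whichever assumption was made.

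For a simple comparison, the claim of 80% power does not hold over the whole stated drop-out range on either sidedness: at 40% drop-out it is 0.64 two-sided and 0.75 one-sided. These sizes assume 102 enrolled per group, the plan's implied inflation of 1.4 and an unadjusted two-group t-test. The power of the planned interaction cannot be computed from the document.

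**What to change.** State the sidedness and the calculation method in the sample-size paragraph of the Design section. Then, depending on what was done:

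- **Two-sided 5%, no correlation assumed:** replace 52 by 64 as the requirement before clustering. Keep N = 204 and restate what it delivers for a simple two-group comparison under the 1.4 inflation: power of about 0.76 at 20% drop-out, 0.71 at 30% and 0.64 at 40%, or a detectable d of about 0.52 to 0.61.
- **One-sided 5%:** declare and justify it, analyse accordingly, and say that power falls to about 0.75 at 40% drop-out.
- **A within-family correlation was used:** state its value and give the power for the planned interaction.

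The cost is wording only, with no extra recruitment. The downside is that the stated power becomes less favourable.

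### The clustering allowance assumes about nine families per region, but the intervention group comes from three areas: power at 73 per group falls below 0.80, and the claim to control regional differences goes too far

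*Protocol article*

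**What the plan says.** The Design section of the protocol article sets the target: "In order to be able to identify at least medium effects (Cohen’s d = 0.5") "with a test power of 0.80 and an alpha error of 0.05", for which "at least 52 families both from the intervention and control group are required to participate in the study". It names region as the level of clustering and concedes that "the extent of the regional variance (hierarchical data structure) can only be estimated". It then applies the allowance: "Assuming 5% intracluster variance explained by the hierarchical data structure, this sample size must be increased by the variance inflation factor", which brings the minimum to 73 per group. An allowance for 20–40% drop-out takes the total to 204, or 102 per group. Neither the number nor the size of the clusters is given.

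The same section recruits intervention families through a care service and its "network partners in three metropolitan areas of Germany (Trier, Saarbrucken and Munich"). Controls come through an umbrella organisation that is said to have regional associations in those areas, but the section ends by saying "Control group participants were recruited throughout Germany".

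Of the multilevel models, the Statistical analysis section says: "This makes it possible to statistically model and control regional differences".

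**The concern.** A variance inflation factor depends on cluster size as well as on the intracluster correlation. The article gives the correlation but leaves out the cluster size. The size that can be inferred from 52 and 73 is much smaller than three areas allow. If region is the cluster, as the text says, the intervention group carries more inflation than was budgeted and the stated power is too high.

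The same layout bears on the analysis. Areas outside the three contain only controls. A model can separate region from group only through controls who live inside the three areas, and their number is not reported. In a non-randomized comparison, a reader who takes the regional-control statement at face value would trust the group contrast more than the design warrants.

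**Working it through.** **Inputs from the Design section:** d = 0.5; power 0.80; alpha 0.05 (sidedness not stated); 52 per group before and 73 after inflation; 102 per group recruited; intracluster correlation (ICC) 0.05; three intervention areas. **Assumptions:** equal split across the three areas (an unequal split would raise the inflation); three scenarios for how controls cluster, because the article does not say.

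**1. Reproducing the plan.**
- Base size, 2(z_α + z_β)²/d²: one-sided 2(1.645 + 0.842)²/0.25 = 49.5, so 50 (51 by t-test); two-sided 63 (64 by t-test). The stated 52 is close to the one-sided figure only.
- Inflation, 1 + (m − 1) × ICC: 73/52 = 1.404, so m = 1 + 0.404/0.05 = 9.1. Check: 52 × (1 + 8 × 0.05) = 72.8, so 73.
- Implied regions per group: 73/9 ≈ 8.

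**2. Inflation with three intervention areas.**
- 73 families: m = 73/3 = 24.3; inflation 1 + 23.3 × 0.05 = 2.17; effective size 73/2.17 = 33.7.
- 102 families: m = 34; inflation 1 + 33 × 0.05 = 2.65; effective size 102/2.65 = 38.5.
- Limit as families are added: 3/0.05 = 60.

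**3. Power**, by Φ(0.5/√[(DE_I + DE_C)/n] − z_α), where DE_I and DE_C are the inflation factors of the intervention and control groups and n is the number analysed per group. Example at n = 73 with unclustered controls: √[(2.17 + 1)/73] = 0.208; 0.5/0.208 = 2.40; Φ(2.40 − 1.645) = 0.775.

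| Scenario | 73, one-sided | 73, two-sided | 102, one-sided | 102, two-sided |
|---|---|---|---|---|
| Plan: clusters of 9 in both groups | 0.82 | 0.72 | 0.92 | 0.86 |
| Three areas; controls unclustered | 0.78 | 0.67 | 0.84 | 0.75 |
| Three areas; control clusters of 9 | 0.73 | 0.62 | 0.81 | 0.71 |
| Three areas in each group | 0.66 | 0.54 | 0.71 | 0.59 |

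These are large-sample values. The few degrees of freedom that three clusters provide would lower them. For example, a cluster-level t-test of three against three regions (4 degrees of freedom) has one-sided power of about 0.52 at 73 per group.

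**4. Size that restores 0.80, best case** (one-sided, controls unclustered): the variance must not exceed [0.5/(1.645 + 0.842)]² = 0.0404. Solving 1.95/n + 0.05/3 = 0.0404 gives n = 82.04, so 83 analysed per group.

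**5. Dependence on the ICC** at 24.3 families per area: inflation is 1.23 at 0.01, 1.47 at 0.02, 2.17 at 0.05 and 3.33 at 0.10. The budgeted 1.40 would fit three areas at an ICC of about 0.404/23.3 = 0.017.

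**6. Region and group.** The intervention group is confined to three areas and controls are nationwide. The within-area comparison therefore rests on controls living in those areas, and the article gives no count of them.

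**The case against.** Several points on the other side have force.

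- **Cluster level.** Nine per cluster could be right for a finer level, such as the network partner. The text, however, names regional variance and no other level.
- **Nationwide controls help the power.** Spreading controls over many regions lowers their inflation. A reader might count nationwide recruitment among the reasons for overstated power, but it works the other way. With unclustered controls the one-sided shortfall at 73 is small (0.78 against 0.80).
- **All 102 analysed.** One-sided power then stays above 0.80 unless controls also sit in few regions. This does not rescue 73, which the plan calls its minimum after drop-out.
- **Repeated measures.** The Statistical analysis section tests group differences through interaction effects. If these are group-by-time terms, stable regional differences largely cancel, and the 5% matters only so far as it applies to change. Adjustment for baseline would also raise power. The plan's own calculation uses neither argument.
- **Mixed causes.** A reader might attribute the whole two-sided shortfall to the three areas. Two-sided power at 73 is already 0.72 with the plan's own inflation; the three areas account for the further fall to 0.54–0.67. Sidedness and the drop-out allowance are separate matters.

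Stronger readings are tempting on the analysis too. One could infer that region cannot be controlled at all. That is unproven, because the control organisation has associations in the three areas and local controls may exist. One could also infer an inflated type I error, or that families sharing a Family Health Partner are left unmodelled. The article does not state its random-effects structure, and such detail belongs in an analysis plan that is not shown. Neither inference is supported.

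**Conclusion.** The sample-size step is wrong as written. An inflation of 1.40 does not fit regional clustering with three intervention areas at the plan's own 5%; the corresponding figures are 2.17 at 73 families and 2.65 at 102. At the plan's minimum of 73 analysed per group, power is below the stated 0.80 in every control scenario examined. The three areas cost about 0.04 to 0.16 one-sided (from 0.82) and 0.05 to 0.19 two-sided (from 0.72).

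This rests on an equal split across areas, an ICC of 0.05 that applies to the tested contrast, and a comparison at a single time point without a few-cluster penalty. At an ICC of 0.01 the inflation at 24 families per area would be 1.23, below what was budgeted.

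On the analysis, region is largely confounded with group, to a degree set by the unreported number of controls in the three areas. The statement on control of regional differences therefore claims more than the design supports; the documents do not show that such control is impossible.

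**What to change.** 1. In the Design section, state the cluster level, the number and size of clusters in each group, and the sidedness of the test.
2. Recompute the inflation separately for each group and restate the power for the families already planned, with a range over the ICC and over how controls cluster. Say whether the 5% refers to levels or to change over time.
3. Narrow the regional-control statement in the Statistical analysis section: the models can account for regional variation only so far as both groups are represented in the same areas. Report how many controls live in the three areas.
4. Using place of residence, already collected according to the Measurements section, add a sensitivity analysis restricted to controls in the three areas, if enough exist.

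A full model with area effects and area-by-time terms should not be required. It would identify the group contrast only from local controls and could leave it barely estimable.

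The cost is wording and a little analysis code, with no additional families. The downside is a less favourable stated power and a sensitivity analysis that is likely to be imprecise.

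### N = 204 keeps the plan's own minimum of 73 families per group only up to about 28% drop-out, although the plan expects 20–40%

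*Protocol article*

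**What the plan says.** The sample size paragraph in Materials and methods, Design, builds the number in three steps.

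1. For an effect of Cohen's d = 0.5, "with a test power of 0.80 and an alpha error of 0.05", the plan states that "at least 52 families both from the intervention and control group are required to participate in the study". It does not say whether the test is one-sided or two-sided.
2. A variance inflation factor is then applied: "Assuming 5% intracluster variance explained by the hierarchical data structure", "resulting in a minimum of 73 families per group". Neither the cluster size nor the factor is given.
3. The last step is drop-out: "With an estimated drop-out rate of 20–40% based on current studies", "the number of samples ultimately increases to a total of N = 204 families". Neither the inflation formula nor the point of the range that was used is given.

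The Methods part of the Abstract confirms equal groups: "Both intervention and control group include 102 families".

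**The concern.** Drop-out is the only step between 73 and 102, so 102 is presented as the enrolment that leaves 73 families per group. For that to be true at drop-out rate q, enrolment must be at least 73/(1 − q). At 20% drop-out 102 is more than enough. In the upper part of the stated range it is not.

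A reader will take the paragraph to mean that 80% power for a medium effect is secured for drop-out anywhere between 20% and 40%. If drop-out ends up near the upper limit, a non-significant result would be read against a power that the design did not have.

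**Working it through.** **Inputs (protocol article, Design and Abstract).** d = 0.5; power 0.80; alpha 0.05; 52 per group before inflation; 73 per group after it; drop-out 20–40%; 204 in total, 102 per group.

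**Reproducing the plan's figures.**
- Variance inflation: 73/52 = 1.404. With 5% intracluster variance this corresponds to about 9 families per cluster: 52 × (1 + 8 × 0.05) = 72.8, rounded to 73. The 9 is back-calculated.
- Drop-out: 73 × 1.40 = 102.2 per group, and 146 × 1.40 = 204.4, which gives 102 and 204.
- Division by (1 − q) at the round rates does not give 204 (see the table). It gives 102 only near 28% (73/0.72 = 101.4), a rate that the article does not name.

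**Enrolment needed and families left.**

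| Drop-out q | Needed per group, 73/(1 − q) | Needed in total | Left per group, 102 × (1 − q) |
|---|---|---|---|
| 20% | 91.25 → 92 | 184 | 81.6 |
| 28% | 101.4 → 102 | 204 | 73.4 |
| 30% | 104.3 → 105 | 210 | 71.4 |
| 40% | 121.7 → 122 | 244 | 61.2 |

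Break-even: 1 − 73/102 = 0.284. At 40% the group is 73 − 61.2 = 11.8 families short, which is 16% of 73.

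**Which sidedness fits the 52.** A two-sample t-test with d = 0.5, alpha 0.05 and power 0.80 needs 50.15, so 51, per group one-sided, and 63.8, so 64, two-sided. The 52 is close to the one-sided figure.

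**Power at d = 0.5.** Two-sample t-test among completers, effective n = families left/1.40, factor held constant after drop-out.

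| Families per group | Effective n | Power, one-sided | Power, two-sided |
|---|---|---|---|
| 73 (plan's minimum) | 52.1 | 0.81 | about 0.71 |
| 71.4 (30% drop-out) | 51.0 | 0.81 | 0.71 |
| 61.2 (40% drop-out) | 43.7 | 0.75 | 0.64 |

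At 80% power, the detectable effect with 61.2 per group is d = 0.54 one-sided and 0.61 two-sided. With the full 73 per group the two-sided value is already 0.55.

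**Sensitivity to the inflation factor.** Assume that the number of clusters stays fixed and their size shrinks in proportion, 9 × 61.2/73 = 7.5. The factor is then 1 + 6.5 × 0.05 = 1.325, and power at 61.2 per group is about 0.77 one-sided and 0.66 two-sided.

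**The case against.** **The formula is inferred.** The article does not show how 102 was reached. Division at about 28%, a rate inside the stated range, also gives 102, and division at the 30% midpoint gives 105, which is not far off. A reader might infer that an arithmetic error is proven. It is not: multiplication by 1.40 is the likelier reading, because 40% is a stated limit and 28% appears nowhere. The shortfall does not depend on this, since 102 × 0.6 = 61.2 however 102 was obtained.

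**The power loss is easily overstated.** A reader might set the two-sided 0.64 against the planned 0.80 and blame drop-out for the whole difference. The documents do not support that. Two-sided power is only about 0.71 with all 73 families present, and that gap comes from the 52. The fall from 73 to 61 costs about 6 points one-sided and about 8 two-sided. On the one-sided basis power still reaches 0.80 at 30% drop-out, so the loss lies towards the upper end of the range.

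**The planned analysis uses more than completers.** Statistical analysis provides for multilevel models over the four time points and for chained-equations imputation when missingness is larger. Families lost after an interim survey can still contribute, so the t-test figures are not the power of the planned analysis. This stands as a limit on the power figures. It does not repair the sizing statement, which counts remaining families and claims no such recovery.

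**Sample size is already declared a limitation.** The Abstract and the Discussion both say so. That weakens the claim of harm, but neither tells the reader that the stated size stops covering the expected drop-out at 28%.

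**Conclusion.** The point holds as a moderate one. The figures 73, 20–40% and 204 do not fit together: 102 per group preserves 73 families up to 28.4% drop-out and falls about 12 families per group short at 40%. This part needs only the printed numbers.

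The consequence for power rests on assumptions: a completer t-test, a one-sided test inferred from the 52, and an inflation factor of about 1.40 back-calculated from 73/52 and held constant. On that basis power at 40% drop-out is about 0.75, against about 0.81 at 73 per group. It would be about 0.77 if clusters shrink as assumed above. The sidedness of the 52 is a separate question and should not be counted as part of the drop-out effect.

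**What to change.** Keep N = 204, and keep 20–40% as the expected drop-out. That estimate comes from other studies, and replacing it with 28% would fit the expectation to the sample size. Add beside it:

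- 102 per group retains the minimum of 73 families up to about 28% drop-out.
- At 40% drop-out about 61 families per group remain. Completer t-test power for d = 0.5 is then about 0.75 one-sided (about 0.81 at 73), with a detectable effect of about d = 0.54, taking the variance inflation as 73/52, about 1.40, unchanged after drop-out.
- Whether the test is one-sided or two-sided. If two-sided, power is about 0.71 at 73 and 0.64 at 61 per group, with a note that the gap at 73 stems from the 52 and not from drop-out.
- The formula and the drop-out rate that were actually used to reach 102.

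Cost: wording only. No further families are needed and no procedure changes, but the stated power becomes less favourable.
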